### Objectives

#### Phase 1: Need assessment.

1. To assess the knowledge, attitude, and practices of healthcare schemes among tribal women in the reproductive age group.2. To understand facilitators and challenges in provision of tribal reproductive age group women healthcare schemes from different stakeholder perspectives.

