### Sampling

East Singhbhum is a district located in the state of Jharkhand. It consists of two sub-divisions, Dalbhum and Ghatsila. Comprising of 11 blocks, Potka, Golmuri cum Jugsalai, Patamda, Ghatsila, Boram, Musabani, Dumaria, Bharagora, Dalbhumgarh, Chakulia, and Gurbandha. A total of twelve villages will be taken from the two randomly selected blocks. The sampling frame for objective one will consists of the list of adolescent girls and reproductive age group women. For the qualitative aspect objective two, the sampling frame will include other stakeholders such as the Block Program Manager/Officer, Block Trainer, Accredited Social Health Activist (ASHA), Auxiliary Nurse Midwifery (ANM), Aanganwadi Workers (AWW), Medical Officer, Village head, and the Tribal women of reproductive age group. Statistical analysis for objective 1 and 3 (feedback form), will be descriptive data analysis and chi-square test to know the association between two variables. Whereas, for objective 2, qualitative data thematic analysis will be done based on codes generated from the transcripts. In objective 1 the study design will be cross-sectional study. Population covered will be the adolescent girls (10–19 years) and reproductive age group (15–49 years) tribal women belonging to following tribes: Santhal, Ho, Munda, Bhumiz, Kharia, and Sabar. Following religion such as Sarna Dharam, Christianity, or Hinduism. Study Participants who will give consent to participate in the study. Migrant population and tribal women suffering from any mental illness will be excluded from the study.

The sample size was calculated through an online tool calculator.net keeping the level of confidence (z) at 95%, and marginal error(E)at 5%, population proportion 50% and population size 258454 [10]. Considering the drop out of 20%, with design effect of 1.5, the sample size becomes 385 (385 + 337) = 722 rounding up to 745. Formula used: n= (Z_1-α/2_)^2 *^ p(1-p)/d^2^. Where n = sample size, Z = level of confidence, E = marginal error, P = Population proportion [11].

Simple random sampling and stratified sampling technique will be used. Out of two blocks, twelve villages will be chosen at random, six village from each block. From each village there will be stratified into two strata, tribal adolescent girls (n = 32/village) and tribal women of reproductive age group. (n = 30 per village). Sampling technique is depicted in form of flow chart mentioned in (Fig 2).

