**Fig 2 pone.0322777.g002:**
[figure not shown]
Simple random sampling and stratified sampling technique.

A Self-administered questionnaire will be used, and in case of illiterate study participants, questionnaire form will be filled by the interviewer/ or the person who will be going to collect the data, on behalf of study participant. Validation of the developed questionnaire will be through the external subject experts and finding the Content Validity Index (CVI) score. Reliability check of the questionnaire will be done through piloting among 10 percent of the study participants from the sample size of the main study and Cronbach’s alpha score will be derived. Domains of the questionnaire will **c**omprise of two sections, Section A- socio-demographic details and section B- Baseline survey consisting of questions on knowledge, attitude, and practices of tribal women towards relevant eight reproductive healthcare schemes of India.

Details of the eight reproductive healthcare schemes included are mentioned in Table 1. Participatory Information Sheet (PIS) will be explained, and Informed Consent (IC) will be taken from the study participants. Data will be collected based on the questionnaire. A total of 20–30 minutes will be given to the study participants and a maximum of 10–15 days per village will be given to collect the data. Quantitative data analysis in terms of frequency, percentage, proportion and for categorical data chi square test will be done. KAP score will be calculated and based on the median and interquartile range which will be finally interpret as low, moderate and high KAP score. All quantitative analysis will be through Jamovi software (Version solid 2.2.5).

**Table 1 pone.0322777.t001:** Healthcare schemes for reproductive age group tribal women in India.

Schemes for Adolescent Girls (10–19 Years)	Schemes for reproductive age group women (15–49 Years)
1.Rashtriya Kishori Swasthya Karyakram	1.Janani Suraksha Yojana
2.POSHAN Abhiyan	2.Janani Sishu Suraksha Karyakaram
3.Anemia Mukt Bharat	3.Pradhan Mantri Matru Vandana Yojana
	4.Pradhan Mantri Surakshit Matritva Abhiyan
	5.Family Planning Schemes under NHM including: a. ASHA Scheme b. Enhanced Compensatory Scheme
	Anemia Mukt Bharat

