## Discussion

Through this study the baseline data (KAP) of health care schemes utilization among tribal women of reproductive age group will be reported also this study will Identify the challenges in the utilization of services from different stakeholder perspectives. Development and Validation of the booklet covering the reproductive healthcare schemes targeted for tribal women will help in increase knowledge among tribal women after the training program on various health schemes (8) mentioned in the booklet. This research would provide valuable insights for policymakers, healthcare providers, and implementers to tailor the programs to the specific needs and preferences of the tribal communities, ensuring their effective utilization and impact. Community at large may benefit from the intervention and recommendations of this study based on the findings. Hence, this study can act as a baseline study based on which some larger studies may be planned to get more generalizable findings.

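### Low, moderate and high KAP cut at the survey's own median and quartiles are relative ranks, so their percentages do not show the level of knowledge, attitude or practice

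*Protocol article*

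**What the plan says.** Objective 1 of the Protocol article (Objectives, Phase 1) is "To assess the knowledge, attitude, and practices of healthcare schemes among tribal women in the reproductive age group". The analysis is described under Methods/design, Sampling, in the text after Fig 2, where a KAP score is to be calculated and classed "based on the median and interquartile range which will be finally interpret as low, moderate and high KAP score". The sentence does not say how the median and interquartile range become two cut-points, how ties are handled, or whether cuts are made per domain or per stratum. It names no fixed threshold.

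The same paragraph plans other outputs: "Quantitative data analysis in terms of frequency, percentage, proportion and for categorical data chi square test will be done". Earlier in Sampling, the analysis for objectives 1 and 3 "will be descriptive data analysis and chi-square test to know the association between two variables".

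The Discussion says that "baseline data (KAP) of health care schemes utilization among tribal women of reproductive age group will be reported" and adds that the study can be the baseline on which larger studies are planned.

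**The concern.** Objective 1 asks about level: how much the women know, what attitudes they hold and what they do. A cut at the sample's own quantiles answers a different question, namely where each woman stands relative to the other respondents. The share called low is then largely decided before any data are seen.

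Two uses of the survey are exposed. A reader of the results could take a low share of about a quarter as evidence on need, when the rule produced it. And a later survey classed by its own quartiles would again show about a quarter low, even if knowledge had really improved, so the class percentages could not register the change.

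**Working it through.** **The plan's own figure.** The article states no expected class shares. Its only numerical target is the sample size, "keeping the level of confidence (z) at 95%, and marginal error(E)at 5%, population proportion 50% and population size 258454", and then "Considering the drop out of 20%, with design effect of 1.5, the sample size becomes 385 (385 + 337) = 722 rounding up to 745". This reproduces: 1.96² × 0.5 × 0.5 / 0.05² = 384.15, taken to 385; 385 × 1.5 = 577.5; 577.5 / 0.8 = 721.9, taken to 722. The allocation of 32 girls and 30 women in each of 12 villages gives 12 × 62 = 744, in line with 745.

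**Do the class shares follow the level?** Scores for 745 respondents were simulated. The true proportion correct was drawn from a beta distribution with parameters 6m and 6(1 − m), where m is the mean. The article gives neither the score distribution nor the number of items, so both are assumptions. Low/moderate/high shares (%) for a continuous score:

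| Rule | m = 20% | m = 50% | m = 80% |
|---|---|---|---|
| Below Q1 / Q1 to Q3 / above Q3 | 25/50/25 | 25/50/25 | 25/50/25 |
| Below median / median to Q3 / above Q3 | 50/25/25 | 50/25/25 | 50/25/25 |
| Median ± interquartile range | 0/86/14 | 8/85/7 | 13/87/0 |
| Fixed at 50% and 75% of maximum (illustration) | 96/4/0 | 51/39/9 | 4/28/68 |

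The median score rose from 0.16 to 0.49 to 0.83 of the maximum. The first two rules show none of this. The third runs the wrong way: the best-informed population has the most low and no high scorers.

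**Discrete scores.** With 20 items and Q1/Q3 cuts, means of 30%, 50% and 70% gave 21/57/21, 22/56/22 and 22/57/21. With 40 items they gave 22/54/23, 23/54/23 and 23/54/22. I also ran 20 items with n = 744, means of 20%, 50% and 80%, and three spreads (beta parameters summing to 4, 6 or 10). Low and high each stayed between 14% and 23%, while the median moved from about 3 to 10 to 17 of 20.

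Near the ends of a short scale, ties move the shares further. Ten items at mean 10% gave 0/82/18 or 52/13/35, depending only on tie handling. Twenty items at mean 90% gave 21/79/0, that is, nobody high.

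**Cost to the association tests.** The only group sizes that the article gives are 12 × 32 = 384 girls and 12 × 30 = 360 women. Assume normal scores, a 0.3 SD difference, independent data and pooled quartile cuts.
- Three-class chi-square: expected shares are 29.6/50.0/20.4% and 20.1/50.0/29.9%. The noncentrality Σ n_g(p_gk − p_k)²/p_k is 13.3; with 2 df (critical value 5.99) power is about 91%.
- t-test on the score: noncentrality 0.3 × √(384 × 360/744) = 4.09; power is about 98%.
- Dividing both groups by the stated design effect of 1.5 (256 and 240) gives about 76% against 92%.

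**The case against.** The strongest reply is that the class is only one output. The article also plans frequencies, percentages and proportions, and the median and interquartile range must be computed to form the classes. All of these describe level directly. That stands. A reader might infer that Objective 1 cannot be answered; the article does not support this.

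A second reply is that the text does not define the cuts. This also stands in part. A reader might infer an exact 25/50/25 split whatever the women know, but that needs Q1/Q3 cuts and few ties, and other readings or floor and ceiling effects give other shares. The reply does not rescue the classes, because under every reading tried the shares are set largely by the rule and not by the level. The full protocol, which is not shown, may hold a more exact scoring rule; the sentence as published points to the sample's own quantiles and to nothing else.

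Third, a reader might infer that the sample was sized for the class shares and that this calculation therefore fails. The article nowhere ties the 50% proportion to the KAP class, and the item proportions are ordinary proportions to which the 5% margin can apply.

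Fourth, relative classes remain valid for comparing subgroups. That is correct. The power loss is real but moderate at the planned group sizes, and a much larger loss would need smaller groups than those the article states.

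**Conclusion.** The point holds within limits. The low/moderate/high percentages, cut as the text is naturally read, do not measure whether KAP is low or high and cannot serve as an absolute baseline. Under Q1/Q3 cuts with few ties, roughly 20–25% fall in each outer class at any level; ties, floor or ceiling effects, or another reading of the rule change those figures without making them informative.

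The rest of the Objective 1 description is unaffected. Using three classes for association tests costs about 7 percentage points of power (91% against 98%) in the example.

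These figures rest on assumed score distributions, numbers of items and a 0.3 SD difference, none of which the article gives. That class shares cut at the sample's own quantiles do not measure level does not depend on those assumptions.

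**What to change.** - Express each domain score (knowledge, attitude, practice) as a percentage of its maximum.
- Make the score distribution (median and interquartile range) and the item- and scheme-level proportions, with confidence intervals, the main Objective 1 result.
- If classes are kept, define them by absolute or externally referenced cut-offs, with tie handling stated, before the score distribution is examined. Survey collection ended on 2 September 2024 (Methods/design), so the distribution may already have been seen; if so, say so and label quartile classes as relative ranks only.
- Test associations on the numeric or ordinal score, allowing for clustering by village.

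The cost is analysis wording; no new data are needed. The drawback is that an absolute cut-off is a convention. The 50% and 75% used above are illustrations and have no source in the article. Any cut-off needs its own justification in each domain, since percentage correct suits knowledge better than attitude or practice.

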### Ethical aspects

This protocol was first approved by the Institutional Scientific Committee (ISC) completed with proposal no: F-2023-20, on 16^th^ August 2023, followed by the Institute Ethics Committee (IEC) on 16 October 2023 till 30 October 2026. Ethical clearance has been done from Institutional Ethics Committee No: MTMC/IEC/2023/53. Permission from the Jharkhand State Tribal Welfare Commissioner, District Civil Surgeon, and gatekeepers (village leaders) were taken. Participation Information Sheet will be explained to the study participants, and written Informed consent will be taken from the reproductive age group tribal women and adolescent girls in presence of the witness before data collection. In case of minor’s parent or guardian written assent/consent will be taken prior to the data collection. The thumb impression will be taken in case of illiterate study participant’s. This study is registered at Clinical Trial Registry-India (CTRI) with CTRI No: CTRI/2024/03/063824 on March 8, 2024. Confidentiality of study participants will be maintained. Name and designation will be coded and will not be exposed.

## Discussion

Through this study the baseline data (KAP) of health care schemes utilization among tribal women of reproductive age group will be reported also this study will Identify the challenges in the utilization of services from different stakeholder perspectives. Development and Validation of the booklet covering the reproductive healthcare schemes targeted for tribal women will help in increase knowledge among tribal women after the training program on various health schemes (8) mentioned in the booklet. This research would provide valuable insights for policymakers, healthcare providers, and implementers to tailor the programs to the specific needs and preferences of the tribal communities, ensuring their effective utilization and impact. Community at large may benefit from the intervention and recommendations of this study based on the findings. Hence, this study can act as a baseline study based on which some larger studies may be planned to get more generalizable findings.

## Abbreviations

ASHA: Accredited Social Health Activist
ANM: Auxiliary Nurse Midwifery
AWW: Aanganwadi Workers
ANC: Antenatal Care
CVI: Content Validity Index
CTRI: Clinical Trial Registry-India
IEC: Institute Ethics Committee
ISC: Institutional Scientific Committee
KAP: Knowledge Attitude Practices
NFHS: National Family Health Survey
MOIC: Medical Officer Incharge
PIS: Participatory Information Sheet
PNC: Postnatal Care
SBA: Skilled Birth Attendants
SRS: Sample Register System
SWOC: Strength Weakness Opportunities Challenges
KAP: Knowledge Attitude Practices
